## Abstract

**Background:** Stroke patients experience chronic hemiparesis in their upper extremities leaving negative effects on quality of life. Robotic therapy is one method to recover arm function, but its research is still in its infancy. Research questions of this study is to investigate how to maximize the benefit of robotic therapy using ReoGo-J for arm hemiplegia in chronic stroke patients.

**Methods:** Design of this study is a multi-center parallel group trial following the prospective, randomized, open-label, blinded endpoint (PROBE) study model. Participants and setting will be 120 chronic stroke patients (over 6 months post-stroke) will be randomly allocated to three different rehabilitation protocols. In this study, the control group will receive 20 min of standard rehabilitation (conventional occupational therapy) and 40 min of self-training (i.e., sanding, placing and stretching). The robotic therapy group will receive 20 min of standard rehabilitation and 40 min of robotic therapy using ReoGo®-J device. The combined therapy group will receive 40 min of robotic therapy and 20 min of constraint-induced movement therapy (protocol to improve upper-limb use in ADL suggests). This study employs the Fugl-Meyer Assessment upper-limb score (primary outcome), other arm function measures and the Stroke Impact Scale score will be measured at baseline, 5 and 10 weeks of the treatment phase. In analysis of this study, we use the mixed effects model for repeated measures to compare changes in outcomes between groups at 5 and 10 Weeks. The registration number of this study is UMIN000022509.

**Conclusions:** This study is a feasible, multi-site randomized controlled trial to examine our hypothesis that combined training protocol could maximize the benefit of robotic therapy and best effective therapeutic strategy for patients with upper-limb hemiparesis.

## Introduction

Severe, persistent paresis occurs in over 40% of stroke patients (1) and is reported to significantly decrease their quality of life (2). Thus, much research has been conducted to develop interventions, with many specifically targeting upper extremity hemiplegia. Among the many examples of neuroscience-based rehabilitation (neuro-rehabilitation) strategies, there is strong evidence supporting robotic therapy, constraint-induced movement therapy (CIMT), and task-oriented training (3, 4).

Robotic therapy is considered an effective intervention for mild to severe hemiplegic arm (5, 6), and is cost-effective for chronic stroke patients in terms of both manpower and medical costs (7, 8). However, its effects may be limited for some patients. Some researchers have found that robotic therapy effectively improves arm function as measured by the Fugl-Meyer Assessment (FMA) (9) and Action research arm test (ARAT) (10), but does not improve the use of the affected arm in activities of daily living (ADL) as measured by the Motor activity log (MAL)-14 (11) and by analysis of data from an accelerometer attached to the affected arm (6, 12–14).

On the contrary, CIMT is the most well-established intervention for improving the use of the affected arm in ADL (15). CIMT consists of three components: (1) a repeated task-oriented approach, (2) a behavioral approach to transfer the function gained during training to actual life (also called the “transfer package”), and (3) constraining use of the affected arm. Some researchers consider the transfer package the most important component of CIMT. In fact, research has shown that usage of the affected arm in daily life is significantly different between patients treated with and without the transfer package component (16, 17). However, many therapists question whether CIMT could benefit their patients because of the shortage of sites possessing the clinical resources to provide the intervention for the long duration required for effectiveness (18).

Therefore, there is an urgent need to establish an effective therapeutic approach, especially for upper-limb hemiplegia during the chronic stage of stroke recovery for which there are few clinical resources (In Japan, the insurance system only allows 260 min per month). Therefore, we will compare the efficacy of several therapy methods. As a control, we will monitor changes in arm function in patients undergoing a short, standard rehabilitation by a therapist and standard self-training (control group). This will be compared to similar self-training including robotic therapy with the ReoGo-J device as an adjuvant therapy (RT group). Finally, the robotic therapy will be compared to combined therapy including robotic therapy and CIMT (CT group). Through these comparisons, we will investigate the effect of robotic therapy, both alone and in combination with CIMT, which we hypothesize will complement each other in chronic stroke rehabilitation. Here, we report the structure and protocol of a multi-center, randomized controlled trial.

## Materials and methods

### Objective

This study is intended to verify the increased efficacy of self-training with robotic therapy compared with the commonly practiced traditional occupational therapy on upper-limb motor function and function in ADL in moderate to severe chronic post-stroke upper-limb hemiplegic patients. In addition, another objective of the study is to verify the degree of superiority of combination training including both robotic therapy and CIMT over training with robotic therapy alone in these patients. Therefore, in this study, primary objective is to compare the RT and control group, secondary objective is to compare the RT and the CT group. Additionally, to compare the CT and control group is auxiliary analysis. We hypothesize that robotic therapy will improve recovery over the usual care alone, and that combining robotic therapy with CIMT will further enhance its benefits.

### Study design

This study will be conducted as a multi-center, prospective, randomized, parallel group study. We aimed to enroll 120 chronic stroke patients from approval by the institutional review board until March 31, 2017. The chronic stroke patients enrolled will be randomized to three groups: a control group to receive conventional occupational therapy (usual care) and self-training that follows the concept of usual care; a group to receive usual care and self-training with robotic therapy; and a group to receive combination training that includes task-oriented training aimed at improving function in ADL and robotic therapy.

The principal investigator will register the study on the clinical trial registration system of the University Hospital Medical Information Network (UMIN000022509) after approval of this study by the clinical research institutional review board of the Hyogo College of Medicine (#2248) and before enrolling subjects.

### Settings

The settings for this study include multiple hospitals and clinics throughout Japan. All sites provide outpatient rehabilitation for stroke patients at the chronic stage of recovery.

### Recruitment

All patients will be screened for the inclusion and exclusion criteria described below. After the patient is determined to meet the criteria, the physician will obtain informed consent from the patient.

### Inclusion and exclusion criteria

Patients will be considered eligible for this study if they are between 20 and 80 years of age, have chronic upper-limb hemiplegia from a supratentorial stroke that occurred at least 6 months before enrollment, are undergoing outpatient or ambulatory rehabilitation, and meet the following functional score requirements: FMA upper-limb scale (9) score of less than 44 points, Stroke Impairment Assessment Set (19) upper-limb distal function score of 1b or above, and modified Ashworth scale (MAS) (20) score of 2 or less.

Patients will be evaluated upon enrollment by their physician, and those with multiple strokes or a cerebellar/brain stem stroke, who have extreme upper-limb pain, or whose upper-limb function is deemed to be improving are not eligible for the study. To avoid complication with other medical conditions, patients with neuromuscular diseases, malignant tumors, balance or gait disturbance, or other serious uncontrolled diseases will be excluded. To ensure patients have the cognitive ability to participate in training and evaluation, patients will be excluded if they have serious aphasia or higher cortical dysfunction (a lack of lucid decision-making ability to participate this study, or a score of 24 points or less on the mini-mental state examination 21). Possible confounding effects of other treatments will be avoided by excluding patients who have received intensive training with an upper-limb training robot or constraint-induced therapy for upper-limb hemiplegia at any time after their stroke, or a botulinum toxin injection within 16 weeks of enrollment. Additionally, before decision-making a participation of study, patients received the standard rehabilitation (physical and occupational therapy) who are not excluded in this study because (1) in study of rehabilitation area for chronic stroke patients, there are few studies that excluse patients receiving the standard rehabilitation before participation of the study from the participant (22–24); (2) in Japan which have health-insurance system that covers all of its citizens, there are few stroke patients in the chronic stroke phase who have not received physical therapy, if they are excluded, the feasibility of this study falls significantly. However, after decision-making a participation of this study, patients were forbidden to receive any other rehabilitation, out of study.

### Withdrawal from study

Patients will be withdrawn from the study if they undergo certain prohibited therapies after enrolling in the study. These include functional electrical stimulation, transcranial magnetic stimulation, and transcranial direct current stimulation. Training with any other upper-limb rehabilitation robot is also prohibited after informed consent. Patients must not receive botulinum toxin injections during the treatment period.

The investigator can decide to withdraw an enrolled and allocated patient from this study if they have difficulty beginning or continuing study participation, such as failure to attend study visits, withdrawal of informed consent, adverse events or complications, recovery of arm function so that no further rehabilitation is needed, or any other event judged by the investigator to warrant withdrawal. The investigators, after withdrawing a subject, shall perform the planned end-of-study examinations to the extent possible and record the observations, last date of training, and reasons for withdrawal on the case report form.

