### Blinding

This study integrates the prospective, randomized, open-label, blinded endpoint (PROBE) study model (25). Because the training methods differ between groups, it is not feasible to blind the subjects, therapists present at the training, and physicians to the treatment. Therefore, the individuals involved in endpoint evaluation, rather than those involved in the treatment, will be blinded. The primary endpoint (FMA) and one of the secondary endpoints (ARAT) will be assessed remotely through audio and visual evaluations of video footage that has undergone blinding. The remaining assessments involve each subject's subjective evaluation, and therefore cannot be blinded, and simple palpation, which will be performed by physicians or therapists who were not present at the training to ensure objectivity.

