### Statistical analyses

Two analysis populations will be established: the safety analysis set and the efficacy analysis set. The safety analysis set will include all patients who were allocated, and the numbers and percentages of safety endpoints will be compared between groups by Fisher's exact test.

The subject characteristics collected upon enrollment will be analyzed by intergroup comparisons of continuous variables by analysis of variance and of categorical variables by Fisher's exact test.

The efficacy analysis set will include all patients for whom primary endpoint data are available based on intention-to-treat principle. Using the mixed effects model for repeated measures, we will perform intergroup comparisons of changes in the FMA upper-limb score at 5 and 10 Weeks of the treatment phase. This model will include the group, time point, group-by-time interaction term, baseline FMA upper-limb score, sex, and botulinum toxin injection. For multiplicity adjustment, Dunnett's test will be employed with the RT group used as a reference. The same analysis will be conducted for the secondary outcomes. The level of significance is set at 0.05.

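### The withdrawal rules do not separate stopping training from leaving the study, so scheduled FMA values can be lost after randomisation for outcome-related reasons

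*Protocol article*

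**What the plan says.** The protocol article's section on withdrawal sets out two routes, both applying after enrolment.

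- **Mandatory:** "Patients will be withdrawn from the study if they undergo certain prohibited therapies after enrolling in the study". The listed therapies include electrical and magnetic stimulation and other upper-limb robots.
- **Discretionary:** the investigator can withdraw an allocated patient for several reasons. They include "recovery of arm function so that no further rehabilitation is needed" and, as a catch-all, "any other event judged by the investigator to warrant withdrawal".

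After either route the investigators "shall perform the planned end-of-study examinations to the extent possible" and record the last training date and the reason. The text does not say when these examinations take place, or whether the week-5 and week-10 assessments continue.

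Three other places bear on this. Under Blinding, "it is not feasible to blind the subjects, therapists present at the training, and physicians to the treatment"; the FMA itself is rated from blinded video. Under Outcomes, everything is measured at baseline, 5 and 10 weeks, and the FMA upper-limb change is primary. Under Statistical analyses, "The efficacy analysis set will include all patients for whom primary endpoint data are available based on intention-to-treat principle", and the analysis is a mixed model for repeated measures at those two visits.

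**The concern.** Recovery of arm function is the construct that the primary endpoint measures. If patients leave the study because the arm has recovered, whether a week-10 value exists depends on what that value would have been. Such departures should be more frequent in the more effective group, and the person deciding knows the allocation. Blinded video rating cannot help where no video was recorded. The best results could then drop out selectively and pull the estimated difference towards zero.

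Withdrawal for a prohibited therapy is a different kind of loss. It removes a patient because of something that happened after randomisation, which an intention-to-treat analysis would normally follow through.

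An analysis plan cannot recover values that the protocol did not require to be collected, so this is not a matter that can be left to it.

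**Working it through.** **The plan's own figures.** The document gives no expected rate of withdrawal for recovery or for prohibited therapy, so there is no stated figure to reproduce. The only allowance for loss is the rise from 39 to 40 per group under Sample size: 1/40 = 2.5%.

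**Inputs from the document (Sample size; Inclusion and exclusion criteria; Outcomes).** Difference 4.25 points, SD 6, 40 per group, entry FMA below 44, maximum 66, visits at weeks 5 and 10.

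**Inputs assumed.** Mean control gain of 3 points at week 10, so 3 + 4.25 = 7.25 in the robotic therapy (RT) group. Week-5 means are half the week-10 means, the correlation between visits is 0.7, and SD 6 applies at both visits. Week 5 is always observed, and every triggered patient is missing at week 10. Where baseline matters, it is uniform from 10 to 43.

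**Estimator.** With week 5 complete, the likelihood estimate of the week-10 difference is

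d10 = b_group + b_5 × (week-5 difference in all patients),

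where b_group and b_5 come from regressing week-10 change on group and week-5 change among those seen at week 10. Baseline is added for the level trigger. Each row below rests on 4,000 simulated trials, with simulation error of about 0.02.

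**Step 1: trigger by level of function.** The protocol's criterion is that no further rehabilitation is needed, which is a level rather than a gain. No cut-off is given, so three are shown.

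| Lost if week-10 FMA would be | Lost, control | Lost, RT | Estimate | Shortfall from 4.25 |
|---|---|---|---|---|
| 50 or above | 2.8% | 7.7% | 4.06 | 0.19/4.25 = 4% |
| 54 or above | 0.8% | 3.0% | 4.14 | 0.11/4.25 = 3% |
| 58 or above | 0.1% | 0.8% | 4.23 | 0.02/4.25 = under 1% |

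**Step 2: extreme case, trigger by size of gain, everyone above it lost.** The share lost is 1 − Φ((c − μ)/6).

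- c = 14: control 1 − Φ(11/6) = 3.3%; RT 1 − Φ(6.75/6) = 13.0%.
- c = 12: control 1 − Φ(9/6) = 6.7%; RT 1 − Φ(4.75/6) = 21.4%.

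The mean among those remaining is μ − 6·φ(a)/Φ(a), with a = (c − μ)/6.

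- c = 14: control 3 − 6(0.0743/0.9666) = 2.54; RT 7.25 − 6(0.2119/0.8697) = 5.79; completer difference 3.25.
- c = 12: control 3 − 6(0.1295/0.9332) = 2.17; RT 7.25 − 6(0.2916/0.7857) = 5.02; completer difference about 2.86.

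The repeated-measures estimate uses week 5 and recovers part of this: 3.70 for c = 14 and 3.42 for c = 12, shortfalls of 0.55/4.25 = 13% and 0.83/4.25 = 20%. If half of the triggered patients still provide a value that stands for week 10, the estimates are 3.99 and 3.90.

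**Step 3: loss explained by week 5.** If patients are lost because the observed week-5 gain exceeds 10 points (8% control, 14% RT), the model estimate is 4.25, so no bias remains.

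**Step 4: prohibited therapy.** Which group would seek such therapies more, and how those patients would have fared, is not stated. No direction can be derived.

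**The case against.** **Timing.** A reader might infer that the post-withdrawal examination happens on the day of withdrawal and so falls outside the model's visits. The text does not say so. The planned end-of-study examinations could equally be the scheduled week-10 assessment, in which case part of the remedy is already there. This stands: the fair criticism is that timing is unstated and the obligation is best-effort.

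**Intention to treat.** A reader might also infer that the withdrawal rules contradict the intention-to-treat statement. They do not. Nothing under Statistical analyses discards withdrawn patients' data or analyses anyone other than as allocated, and a withdrawn patient with some endpoint value can stay in the efficacy set. The claim is weakened only to the extent that values are never collected.

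**The model.** It would be too strong to say that the mixed model cannot repair the loss. Step 3 shows that it can when week-5 values explain the loss, and an investigator acting on visible improvement is acting partly on what week 5 shows. What remains is recovery judged on function not captured at a scheduled visit.

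**Size.** The gain-based case is a poor match to the protocol's wording. A patient entering at 20 who gains 14 reaches 34, still under the trial's own entry ceiling of 44, and would hardly be called recovered. Entry also requires at least 6 months since stroke and excludes patients judged to be improving. Recovery to the point of needing no rehabilitation is probably rare here. This also stands, and is why the level-based figures carry more weight.

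None of this removes the basic point: the document makes leaving the study, rather than stopping training, the consequence of these events.

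**Conclusion.** The concern holds as a weakness in how follow-up is fixed. The withdrawal rules allow, and for prohibited therapies require, removal from the study after randomisation. They do not secure the week-5 and week-10 FMA in those patients.

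For recovery, the bias runs towards a smaller difference if RT works, and it is probably small: about 4.1 to 4.2 instead of 4.25 when about 1% to 8% of the RT group is lost on reaching FMA 50 to 58 or above. The range of about 3.4 to 3.7 requires that everyone gaining more than 12 to 14 points is lost, with no later value obtained; it is a bound for illustration, not a forecast. All these figures rest on the assumed control gain, correlation, baseline spread and complete loss of triggered patients. For prohibited therapies neither size nor direction can be stated.

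This is a cheap improvement worth making, not an error that invalidates the primary comparison.

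**What to change.** In the withdrawal section, separate the two events and state that:

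- stopping the assigned training, or receiving a prohibited therapy, does not end outcome assessment;
- the blinded-video FMA and the other outcomes are still collected at the scheduled week-5 and week-10 visits in every allocated patient who has not withdrawn consent to assessment;
- these values enter the primary analysis in the group to which the patient was allocated.

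The recording of the last training date and the reason is already required and should stay. No change is proposed to when or why training is stopped.

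The cost is a few sentences of protocol wording and some effort to bring back patients who have stopped training. No visit is added beyond those already scheduled.

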### Enrollment and randomization

Subjects who meet all of the inclusion criteria and none of the exclusion criteria, and have given informed consent, will be evaluated by the investigators for enrollment. At enrollment, information will be collected including demographic data, body measurements, stroke information, complications, lifestyle factors, and baseline function measures. The investigator will verify that the patient is eligible to participate and enter information into the electronic data capture and web allocation system as required.

Randomization will be done through the web allocation system. The patients will be randomized to one of the three treatment groups using dynamic allocation by the minimization method based on the baseline FMA upper-limb score, center, period after stroke, and age.

### Blinding

This study integrates the prospective, randomized, open-label, blinded endpoint (PROBE) study model (25). Because the training methods differ between groups, it is not feasible to blind the subjects, therapists present at the training, and physicians to the treatment. Therefore, the individuals involved in endpoint evaluation, rather than those involved in the treatment, will be blinded. The primary endpoint (FMA) and one of the secondary endpoints (ARAT) will be assessed remotely through audio and visual evaluations of video footage that has undergone blinding. The remaining assessments involve each subject's subjective evaluation, and therefore cannot be blinded, and simple palpation, which will be performed by physicians or therapists who were not present at the training to ensure objectivity.

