### Outcomes

All outcomes will be measured at baseline, 5 and 10 weeks. The primary outcome examined will be changes in the FMA upper-limb score (9). This assessment examines motor and joint function, balance, and sensation in hemiplegic patients and results are represented as a numerical score with a maximum of 66 points.

Secondary outcomes include changes in: (1) the “amount of use” and “quality of movement” components of the MAL-14 scale (11), which assesses limb function in ADL; (2) the individual components of the FMA (9); (3) the ARAT score, another measure of upper-limb function (10); (4) the motricity index (26), an assessment of muscle strength in stroke patients; (5) the MAS score (20), which assesses muscle tone (i.e., spasticity); (6) the active range of motion of the shoulder, elbow, forearm, wrist, and fingers (27); and (7) the Stroke Impact Scale (28), a quality of life assessment scale for stroke patients.

Safety outcomes will include the occurrence of any adverse events. Adverse events will be assessed as either related or unrelated to the study treatment, and their severity graded using the CTCAE Ver 4.03 (29) as a reference. All adverse events will be recorded on the medical chart and case report form. In the case of serious adverse events, including those that are life-threatening or result in hospitalization, a “serious adverse event and malfunction report” will be prepared by the investigator and submitted to the hospital director promptly.

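### For motricity index, modified Ashworth scale and active range of motion, the stated safeguard is absence from training, which does not assure masking to allocation

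*Protocol article*

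**What the plan says.** The Blinding section adopts an open-label design with blinded endpoints: "This study integrates the prospective, randomized, open-label, blinded endpoint (PROBE) study model". It explains that "it is not feasible to blind the subjects, therapists present at the training, and physicians to the treatment", and concludes that "the individuals involved in endpoint evaluation, rather than those involved in the treatment, will be blinded".

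It then gives the arrangements by type of assessment:

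- FMA (primary) and ARAT (secondary) "will be assessed remotely through audio and visual evaluations of video footage that has undergone blinding".
- Everything else is described in one sentence: "The remaining assessments involve each subject's subjective evaluation, and therefore cannot be blinded, and simple palpation". The palpation part is to be "performed by physicians or therapists who were not present at the training to ensure objectivity".

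The Outcomes section lists seven secondary outcomes. They include "4) the motricity index (26), an assessment of muscle strength in stroke patients; (5) the MAS score (20), which assesses muscle tone", and "the active range of motion of the shoulder, elbow, forearm, wrist, and fingers". The Statistical analyses section applies the primary outcome's analysis to the secondary outcomes: a mixed model for repeated measures, with Dunnett's test taking RT as reference. The limitations at the end of the Discussion mention that patients cannot be blinded and say nothing about assessors.

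**The concern.** The credibility of a PROBE trial rests on its assessors not knowing the arm. For the hands-on assessments the only stated condition is that the rater did not attend the training. That separates the rater from the delivery of treatment, but it does not prevent the rater from knowing which treatment was given.

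Muscle tone, strength and range of movement are scored by a clinician's judgement or measurement. A rater who knows the arm and expects the robot to help could score slightly in its favour. The planned model cannot tell such a shift from a treatment effect. A reader who sees the PROBE label, and a limitations paragraph that mentions only patients, could take these comparisons to be as well protected as FMA and ARAT.

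**Working it through.** **Step 1: which outcomes fall under the weaker rule.** The Blinding section does not name them, so they are found by elimination from the seven secondary outcomes.

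| Secondary outcome | Arrangement in Blinding |
|---|---|
| MAL-14 | Subject's own evaluation; stated as impossible to blind |
| FMA components | Blinded video, as part of FMA |
| ARAT | Blinded video |
| Motricity index | Not named; left for the palpation category |
| MAS | Not named; left for the palpation category |
| Active range of motion | Not named; left over, though neither self-report nor palpation in the ordinary sense |
| Stroke Impact Scale | Subject's own evaluation; stated as impossible to blind |

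Three of seven remain.

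**Step 2: whether the statements fit together.**

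- General statement: endpoint evaluators will be blinded.
- Specific rule for the three outcomes: the rater was absent from training. Masking to allocation is not mentioned.
- Permitted raters: physicians or therapists. The infeasibility statement limits therapists to those present at training but puts no such limit on physicians. One permitted class of rater is thus a class that the section says cannot feasibly be blinded.

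The general statement and the specific rule do not secure the same thing.

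**Step 3: illustration of size.** The protocol gives no figure for rater bias, so there is none to reproduce. The bias values below are assumptions.

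Inputs:
- 40 per group (Sample size) and three groups.
- Dunnett's test with RT as reference, level 0.05 (Statistical analyses), taken as two-sided as in Sample size. This gives two comparisons, control and CT each against RT.
- Assumed pure rating bias d = 0.1, 0.2 or 0.3 SD in favour of RT over control, with no true effect.
- Simplification: a single time point with equal groups, so degrees of freedom are 3 × 40 − 3 = 117 and the two contrasts have correlation 0.5. The planned repeated-measures model with covariates will differ somewhat.

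Critical value c: solve P(|T1| < c and |T2| < c) = 0.95 for a bivariate t with correlation 0.5 and 117 degrees of freedom. This gives c = 2.239. The level of one comparison is 2 × P(T > 2.239) = 0.027.

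Non-centrality under bias d: d × √(40/2) = d × 4.472.

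Rejection rate: P(T′ > 2.239) + P(T′ < −2.239), where T′ is non-central t with 117 degrees of freedom.

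| Assumed bias (SD) | Non-centrality | False-positive rate, RT vs control |
|---|---|---|
| 0 | 0 | 2.7% |
| 0.1 | 0.447 | about 4% (0.0425) |
| 0.2 | 0.894 | about 9% (0.093) |
| 0.3 | 1.342 | about 19% (0.189) |

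**The case against.** The strongest reply is that the general sentence already covers every endpoint evaluator, and that absence from training is simply how it is carried out for hands-on tests. The words about what cannot be blinded attach to the subjects' own evaluations, not to palpation. This stands in part: a reader might infer that these raters are unmasked, and the document does not say so. It supports only that masking is not assured, because the specific rule is weaker than the general promise and admits physicians.

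Second, assigning the three outcomes to palpation is an inference, and the poor fit for range of motion may be loose wording. This also stands, although no other listed arrangement fits them.

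Third, an article leaves operating procedures to the full protocol. That is fair for matters such as rater access to records. But the article does state the rule for these raters, and the rule it states is not masking.

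Fourth, a reader might calculate the inflation with an unadjusted two-sample t-test (40 per group, two-sided 0.05) and obtain 7%, 14% and 26%. The protocol does not support those figures, because it plans Dunnett's test and the same analysis for secondary outcomes. Under that test the rate at 0.1 SD stays below 5%.

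Finally, tone and strength need hands-on testing, so remote video is no substitute, and separate raters are a real, if partial, safeguard.

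**Conclusion.** The point holds in a limited form. The Blinding section assures masking for FMA and ARAT. For motricity index, MAS and active range of motion it assures only that the rater was not at the training. Assessor bias in these three secondary outcomes is not excluded, and the limitations do not say so. The primary outcome, and the primary comparison on which the sample size rests, are untouched.

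How far this matters depends on a bias that the documents neither quantify nor show to exist. Both the 0.1 to 0.3 SD range and its direction towards RT are assumptions, and the calculated rates show sensitivity rather than an expected error. The conclusion also rests on the elimination in step 1. If the full protocol masks these raters, the remaining defect is that the article describes a weaker rule than the one in force.

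**What to change.** In the Blinding section, extend the condition on these raters: they should be both absent from training and kept unaware of allocation. Name the three outcomes to which this applies, and reconcile the admission of physicians as raters with the statement that physicians cannot feasibly be blinded. Record any unmasking on the case report form. Where practical, film active range of motion in the same session as FMA and ARAT for the same remote blinded rating.

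If a site cannot achieve masking, report these outcomes as not assuredly blinded and add this to the limitations in the Discussion.

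The cost is small. Separate raters are already planned, so no extra staff are needed, and one case-report-form item is added. Optional filming takes a few more minutes. Masking will sometimes fail at small sites, but those failures will then be recorded.
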